### Relevant concomitant care permitted or prohibited during the trial {11d}

All participants cannot receive any other neoadjuvant treatments outside of the trial. Steroid use is allowed when immune-related AE occurrs.

### Provisions for post-trial care {30}

Regular follow-up is planned in post-trial care. An insurance for this trial will cover the compensation to participants who suffer harm from trial participants if the AE is determined as treatment-related.

### Outcomes {12}

The primary endpoint is the 1-year RFS rate, defined as the time period from randomization to the first documented HCC recurrence or death from any cause. The key secondary endpoints include pathological remission degree and OS which was defined as the time period from randomization to death from any cause. Pathological complete remission (pCR) is defined as existent ≤ 1% active tumor cells, while major pathological remission (mPR) is defined as ≤10% active tumor cells. Safety outcomes encompass adverse events (AEs), defined as the occurrence of ≥ 3 grade hematological or non-hematological toxicities (including but not limited to liver dysfunction, hematological abnormalities, hypertension, diarrhea, proteinuria, hand-foot syndrome, etc.). The severity of adverse events will be graded according to the Common Terminology Criteria for Adverse Events (CTCAE v5.0).

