**Methods:**

This multi-center, open-label randomized phase 3 trial will be conducted at 7 tertiary hospitals. Patients with single huge (≥ 10 cm in diameter), resectable HCC will be randomly assigned in a 1:1 ratio to arm of surgery alone or arm of neoadjuvant therapy followed by surgery. In the neoadjuvant therapy group, patients will receive TACE within 1 week after randomization, followed by camrelizumab (200 mg q2w, 4 cycles), along with apatinib (250 mg qd, 2 months). Patients will receive liver resection after neoadjuvant therapy unless the disease is assessed as progressive. The primary outcome is recurrence-free survival (RFS) at 1 year. The planned sample size of 60 patients will be calculated to permit the accumulation of sufficient RFS events in 1 year to achieve 80% power for the RFS primary endpoint.

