### Sample size {14}

The sample size was performed using the software PASS (version 2015). The calculation is based on the primary endpoint which is RFS in the present study. Previous research data showed that the 1-year RFS rate was 40% for patients with a single huge HCC after surgery [9]. Our prior study showed that the 1-year event-free survival (EFS) rate was 65% for patients with unresectable HCC after receiving a similar treatment regime [22]. Therefore, we hypothesize that neoadjuvant therapy could increase the 1-year RFS rate to 70% for patients with a single huge HCC. Using an alpha of 0.025 at one-sided, a power of 80%, a total of 60 participants needed to be enrolled with 30 in each arm when considering an attrition rate of 10% and an anticipated recruitment period of 1.5 years.

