## Statistical methods

### Statistical methods for primary and secondary outcomes {20a}

Primary efficacy will be assessed in all randomized patients using the intention-to-treat (ITT) principal. And the safety analysis will include all participants who received at least one post-randomization measure. Kaplan-Meier method is used to determine RFS and OS. Hazard ratios (HRs) with 95% confidence intervals (CIs) are estimated using Cox proportional risk models. Continuous variables are analyzed using either unpaired Student’s *t*-test or the Mann-Whitney *U* test, while categorical data are assessed using the chi-square test or Fisher’s exact test, as appropriate. Data analysis will be performed using SPSS version 26.0 and *P* values < 0.05 are considered statistically significant. The flow of participants screened by the trial and trial results will be reported according to Consolidated Standards of Reporting Trials (CONSORT).

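### The primary endpoint is named as a 1-year RFS rate but defined as a time to event, and the stated 80% power is approached only under the second reading with follow-up beyond 12 months

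*Protocol article*

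**What the plan says.** All places are in the protocol article.

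- **Outcomes {12}** gives the definition as follows: "The primary endpoint is the 1-year RFS rate, defined as the time period from randomization to the first documented HCC recurrence or death from any" (final word omitted). The name is a rate and the definition is a time.
- **Abstract, Methods:** "The primary outcome is recurrence-free survival (RFS) at 1 year". The sample size is said there "to permit the accumulation of sufficient RFS events in 1 year to achieve 80% power for the RFS primary endpoint".
- **Table 1 (Participant timeline {13}):** the primary endpoint is marked at month 12, which is also the last tabulated visit.
- **Sample size {14}:** "The calculation is based on the primary endpoint which is RFS in the present study". The inputs are two 1-year figures. For control, "the 1-year RFS rate was 40% for patients with a single huge HCC after surgery", and 70% is hypothesized for the neoadjuvant arm. Alpha is 0.025 one-sided, power 80%, attrition 10%, and 60 patients are to be enrolled.
- **Statistical methods {20a}:** Kaplan-Meier is assigned to RFS and OS, and "Hazard ratios (HRs) with 95% confidence intervals (CIs) are estimated using Cox proportional risk models". No time point is attached and no result is named as decisive.
- **Interim analyses {21b}:** the trial may stop if the RFS null hypothesis is rejected. The section does not say whether that null concerns the 1-year rate or the whole curve.
- **Recruitment {15}:** the study runs from January 2024 to June 2026.

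**The concern.** A difference in 12-month RFS and a hazard ratio over all follow-up answer different questions. The first compares the two curves at one point and ignores their shape before it and everything after it. The second averages the effect over the whole of follow-up and, as a single summary, relies on proportional hazards. With 30 patients per arm the two can lead to different conclusions from the same data.

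Two things are at stake. First, what counts as a positive trial is not settled by the endpoint definition. In an open-label trial that should be settled before outcome data are seen. Second, the two readings have different power, so the adequacy of 60 patients depends on which one is meant.

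**Working it through.** **Inputs from the article.** 1-year RFS 40% versus 70%; one-sided alpha 0.025 (the same as two-sided 0.05); power 80%; 1:1 allocation; 60 patients, or 60 × 0.9 = 54 after 10% attrition; recruitment over 1.5 years; study end June 2026, so about 1 year of follow-up after the last patient.

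**Assumptions not in the article.** Exponential RFS times, uniform accrual, and random loss of 10% per year (0% also shown).

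**Step 1. The stated 60 under the time-to-event reading.**
- Implied hazard ratio = ln 0.70 / ln 0.40 = 0.389.
- Schoenfeld events = 4 × (1.960 + 0.842)² / (ln 0.389)² = 4 × 7.849 / 0.890 = 35.3, so 36.
- Event probability with 1.5 years of accrual and 1 further year: 0.783 in control and 0.458 in the neoadjuvant arm, mean 0.620.
- Patients: 36 / 0.620 = 58.1, so 58-60 before attrition and 64-68 after dividing by 0.9.
- Power: 82% with 60 patients and 78% with 54.

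So 60 is about right before attrition and slightly short after it.

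**Step 2. The same inputs under the 1-year-rate reading.**
- Two-proportion formula, pooled: [1.960 × √(2 × 0.55 × 0.45) + 0.842 × √(0.24 + 0.21)]² / 0.30² = (1.379 + 0.565)² / 0.09 = 42 per arm.
- Total 84, or 84 / 0.9 = 94 after attrition. The unpooled variant gives 90 and the continuity-corrected one 110.
- Power with 60: Φ[(0.30 × √30 − 1.379) / 0.671] = Φ(0.39) = 65%. With 54 (27 per arm): 61%.

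**Step 3. Log-rank restricted to the first 12 months**, which is how the abstract's phrase about events in 1 year can be read.
- Mean event probability = (0.60 + 0.30) / 2 = 0.45, so 60 patients give 27 events.
- Power: 69% with 60 and 64% with 54.

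**Step 4. Simulation of both analyses on the same data.** 30 per arm, 10% yearly loss. For the longer follow-up, accrual lasts 17.5 months (1 January 2024 to 15 June 2025) and closure is at 29.5 months. The 12-month difference is the Kaplan-Meier difference with Greenwood variance. All tests are two-sided at 5%.

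| | RFS followed to mid-2026 | RFS censored at month 12 |
|---|---|---|
| Power, log-rank | about 78% | about 65% |
| Power, 12-month difference | about 66% | about 66% |
| Verdicts differ (40% vs 70%) | about 18% | about 7% |

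With no loss to follow-up, the log-rank power becomes 81% (mid-2026) and 68% (month 12). The 12-month difference stays at 66-67%, and the verdicts differ in about 20% and 5% of trials.

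**Step 5. Equal arms (40% versus 40%).** The chance that at least one of the two tests is significant is about 7-9% across the follow-up scenarios. The 12-month Greenwood test alone rejects in about 6%, because its variance is somewhat too small at 30 per arm. Only the remainder, roughly 1-3 percentage points, comes from having two routes to success.

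**The case against.** **The deciding test may be in an analysis plan that is not shown, and a journal article is condensed.** This stands as far as it goes: the absence of a named test is not the point here. The endpoint definition does belong in this document, however, and it is given in two incompatible forms. A later plan that names a test would have to depart from one half of the Outcomes sentence.

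**The sentence can be harmonized.** RFS could be the time variable and its Kaplan-Meier value at 1 year the summary, with the hazard ratio alongside. That is a fair reading, but power is then about 66%, and the 80% claim in Sample size {14} does not hold for it.

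**A reader might infer that a chi-square or Fisher test is planned for the 1-year rate.** The article does not support that. The sentence "categorical data are assessed using the chi-square test or Fisher’s exact test, as appropriate" is generic and tied to no outcome; pathological response, adverse events and baseline data are its natural targets. For RFS the article names only Kaplan-Meier and Cox.

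**A reader might infer that the two analyses often give opposite verdicts.** That is too strong. The 18% needs RFS follow-up to mid-2026, whereas Table 1 ends at month 12. With censoring there, the figure is about 7%. The June 2026 end date makes longer follow-up possible, and the article states no censoring at 12 months, so both ends of the range belong in the statement.

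**Choosing the favourable result is nowhere permitted.** Correct. The error inflation is a risk if the choice stays open, and it is modest.

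**Conclusion.** The contradiction is real and lies within one sentence; no other section resolves it. Its main consequence is for power. The stated 80% is approached (78-82%) only if RFS is analysed as a time to event with follow-up beyond 12 months. For the endpoint as the abstract and Outcomes {12} name it, power is about 61-66%. For a log-rank test censored at the last tabulated visit it is about 64-69%. The secondary consequence is that the two analyses differ in about 7-18% of trials under the design effect with 10% yearly loss, and that accepting either would give a two-sided error of about 7-9%.

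These sizes rest on exponential times, uniform accrual and 0-10% yearly loss, none of which the article specifies. The contradiction itself does not depend on them.

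**What to change.** Name one estimand and one primary test, and use them in the abstract, Outcomes {12}, Sample size {14}, Statistical methods {20a} and Interim analyses {21b}. Decide before outcome data are reviewed.

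**Option (a), time to event.** Define the primary endpoint as RFS, measured from randomization to first documented recurrence or death from any cause. Compare arms by one log-rank test at two-sided 5%, with the Cox hazard ratio as the effect measure and 12-month Kaplan-Meier RFS per arm as descriptive. State the data cut, and extend RFS assessment in Table 1 past month 12 to that cut. That extra assessment is the cost. Without it, power must be restated as about 65%.

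**Option (b), 1-year rate.** Define the primary endpoint as RFS at 12 months. Make the Kaplan-Meier difference at 12 months the sole primary test and the hazard ratio supportive. Restate power for 60 patients as about 61-66%. No assessments beyond Table 1 are needed; the cost is a lower stated power, or about 90-110 patients if 80% is to be kept.

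Under either option, show the sample-size calculation for the test chosen, and say that the interim RFS hypothesis is the same one.

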### Intervention description {11a}

Patients in the control arm will undergo liver resection within 1 week after randomization. Patients in the arm of neoadjuvant therapy will receive TACE within 1 week after randomization, followed by camrelizumab (200 mg q2w, for 4 cycles). They were also given oral apatinib mesylate tablets (250 mg qd, for 2 months). Patients must undergo imaging tests, including computed tomography (CT) scans of the chest/abdomen/pelvis, within 28 days before their first dose of medication. Additional scans of other body areas may be conducted if clinically necessary. After neoadjuvant therapy, a preoperative assessment including a CT scan will be conducted within 14 days (± 7 days) after the last dose of medication. Patients will receive surgery after neoadjuvant therapy if the disease is not assessed as progressive disease. To ensure the safety of the surgery, camrelizumab is discontinued for at least 2 weeks, while apatinib is discontinued for at least 1 week before the surgery.

All TACE procedures were performed by experienced physicians and a uniform treatment protocol was applied to each patient [21]. TACE was performed through the right femoral artery with local anesthesia. After arteriography of the celiac trunk and superior mesenteric artery to visualize arterial vascularization of the liver, body surface-dependent doses of the chemotherapeutic agents 5-fuorouracil (800~1000 mg) and epirubicin-adriamycin (30~40 mg) were injected. Subsequently, lipiodol and polyvinyl alcohol foam embolization particles were injected as selectively as possible into the hepatic segmental artery at the target tumor location. The embolization agent doses ranged from 5 to 30mL and were determined based on the tumor location, size, and number.

The dosages of apatinib and camrelizumab in this study will be selected based on recommended dosages in their drug labels and prior clinical studies for unresectable HCC [13].

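### As worded, the primary RFS endpoint leaves a neoadjuvant patient who progresses or is never resected event-free until death, which tilts the comparison towards the experimental arm

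*Protocol article*

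**What the plan says.** Outcomes {12} gives the primary endpoint as the 1-year RFS rate, "defined as the time period from randomization to the first documented HCC recurrence or death from any cause". No other event is listed.

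Intervention description {11a} sets different paths to surgery:
- Control: "Patients in the control arm will undergo liver resection within 1 week after randomization".
- Neoadjuvant: TACE, then four two-weekly cycles of camrelizumab and 2 months of apatinib, then "a preoperative assessment including a CT scan will be conducted within 14 days (± 7 days) after the last dose of medication". After that, "Patients will receive surgery after neoadjuvant therapy if the disease is not assessed as progressive disease". Apatinib is stopped at least 1 week, and camrelizumab at least 2 weeks, before the operation.

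On the population, Statistical methods {20a} says "Primary efficacy will be assessed in all randomized patients using the intention-to-treat (ITT) principal". The section on non-adherence and missing data {20c} confirms that non-adherent patients stay in the primary analysis.

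Sample size {14} takes the control figure from a surgical series ("the 1-year RFS rate was 40% for patients with a single huge HCC after surgery"). It supports the 70% target for the neoadjuvant arm with a different endpoint in unresectable disease: "the 1-year event-free survival (EFS) rate was 65" per cent.

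**The concern.** Recurrence presupposes that the tumour was removed. Only the neoadjuvant arm has a long period before surgery, and only there does progression bar the patient from surgery. A patient who progresses during that period keeps the tumour, so the only event left in the definition is death. The regimen's clearest failure is then scored as a success for as long as the patient lives.

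The wording has a second, separate consequence. A control patient can have a recurrence from about week 1. A neoadjuvant patient cannot have one until after the operation, some 10 weeks or more after randomization.

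Both features push the same way. With 30 patients per arm, a couple of patients classified one way or the other can matter to the result.

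**Working it through.** **1. The plan's own figure.** Inputs from Sample size {14} and Recruitment {15}: 40% vs 70% at 1 year, one-sided alpha 0.025, power 80%, 1.5 years' accrual, study length 2.5 years, 10% attrition.
- Exponential survival: HR = ln 0.7 / ln 0.4 = 0.389.
- Schoenfeld events: 4 × (1.960 + 0.842)² / (ln 0.389)² = 35.3.
- Average event probability, with 10% loss per year: 0.576.
- N = 35.3 / 0.576 = 61.2, so 62. With 60 patients, power is 79%.

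The stated 60 is therefore reproduced to within 2 patients and is not in dispute here.

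**2. Progressors who are never resected.** Let f be their share of the neoadjuvant arm. The protocol gives no f for this regimen and population. The nearest figure is in Background {6a}: 94.4% of patients reached surgery in a phase II trial of the two drugs, so 100 − 94.4 = 5.6% did not. That is 0.056 × 30 = 1.7 patients per arm. A value of 10% is a further assumption.

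Against an analysis that counts them as failures, the apparent 1-year rate rises by f × (share of them alive at 1 year), so by at most f: from 40% to 45.6% at f = 5.6%, or to 50% at f = 10%.

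One-sided log-rank error was simulated with 30 per arm, 1.5 years' accrual, 2.5 years in total and 20,000 runs. The null is a true 1-year rate of 40% in both arms with progression counted. Progression occurs at 0.2 years, and median survival afterwards is 1 to 2 years (assumed).

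| f | progression counted | event-free until death | censored at progression |
|---|---|---|---|
| 5.6% | 2.7% | 5.2-5.9% | 4.5% |
| 10% | 2.7% | 7.9-11.1% | 7.3% |

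Counting progression brings the error back close to the nominal 2.5%. Censoring does not.

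**3. Later surgery alone, with no progressors.** Two months of drug is about 8.7 weeks. Adding at least 1 week off apatinib gives about 10 weeks. Adding the latest assessment scan (14 + 7 days) gives about 12 weeks. Assume no events before surgery and the control hazard, −ln 0.40 = 0.916 per year, after resection in both arms. With surgery delayed by d years, S(1 year) = exp(−0.916 × (1 − d)):
- d = 10/52: exp(−0.740) = 0.477.
- d = 12/52: exp(−0.705) = 0.494.

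The contrast is thus 48-49% against 40% with no effect on the hazard after resection. One-sided rejection with 27 per arm (30 less 10%) is about 13% and 17% with 12 months' follow-up, and about 11% and 14% with follow-up to June 2026.

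**4. The two components do not simply add.** In the model of step 3, if a fraction f is unresected and alive at 1 year, the rate is f + (1 − f) × 0.477. The extra gain is f × 0.523: 2.9 points at f = 5.6% and 5.2 points at f = 10%.

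**5. What an event-free survival endpoint would repair.** Rerunning step 3 with unresected patients counted as events at the planned date of surgery gives rejection of 8.4% (10 weeks) and 11.6% (12 weeks) at f = 5.6%, and 5.2-7.4% at f = 10%. The part due to delay remains.

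**The case against.** The strongest reply is that the text does not say how these patients are classified. Investigators may record progression before surgery as recurrence, and the first component then disappears for progressors. The use of an EFS rate to support an RFS target suggests loose terminology rather than a deliberate exclusion. This stands as a limit on certainty, but it does not rescue the wording. The definition is stated with a closed list of events, and the trial is open-label, so classification should not rest on an unwritten convention.

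Also standing: death from any cause counts from randomization, so unresected patients do become events when they die, and deaths before surgery reduce the delay effect. The 5.6% covers non-resection for any reason, in BCLC B/C disease, without TACE.

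A reader might be tempted to go further on four points that the document does not support:
- That the 11-17% rejection rate measures the effect of unresected progressors. It comes from a model with none and reflects delay only.
- That non-resection adds a full 5.6 or 10 points on top of 48-49%. Step 4 gives about 3 or 5.
- That a new lesion on the Week 9 CT is an event in one arm and not in the other. Table 1 does not assign that scan to an arm, and {11a} and {18a} describe such a scan only after neoadjuvant therapy. If controls are not scanned then, their early recurrences are detected later and the early asymmetry is smaller than modelled.
- That event-free survival removes the whole bias. Step 5 shows that it does not.

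**Conclusion.** The point holds as a defect in a stated definition. Followed as written, the primary endpoint keeps neoadjuvant patients who progress or are never resected event-free until death, and this biases the comparison towards the experimental arm unless progression is recorded as recurrence.

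The size is conditional on a rate that the protocol does not give. At 5.6% non-resection, one-sided error is about twice nominal; at 10%, it is roughly three to four times nominal. Both rest on an assumed median survival of 1 to 2 years after progression.

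The effect of later surgery is a separate, upper scenario. It requires no deaths before surgery, equal hazards after resection, and recurrences dated when they occur. It should not be presented as the effect of the missing events. Nothing here shows that a positive result would be false; it shows that the endpoint cannot exclude that explanation.

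**What to change.** Define the primary endpoint as event-free survival from randomization, with the same rules in both arms. The event is the first of:
- progression that precludes resection, dated at the scan that shows it;
- failure to achieve resection for any reason, dated by one rule prespecified for both arms;
- recurrence after resection;
- death from any cause.

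Add residual tumour at resection to the list only if that status is recorded. {18a} mentions intraoperative information but does not name it.

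Restate the 40% and 70% assumptions for this endpoint and recheck the sample size. Report RFS from the date of resection among resected patients as a supportive analysis, labelled non-randomised. State openly that the new endpoint does not remove the part of any difference that comes only from later surgery.

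The cost is a protocol and registry amendment and a less favourable expected rate in the experimental arm. No treatment rule changes.

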### Objectives {7}

The study aims to (1) directly compare the efficacy of neoadjuvant therapy followed by surgery and surgery alone on HCC recurrence risk and survival in patients with single huge HCC; (2) explore the safety of neoadjuvant therapy regimen of TACE, camrelizumab, and apatinib; and (3) offer evidence and guidance for neoadjuvant therapy strategy in HCC patients with a high risk of recurrence.

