## Data collection and management

### Plans for assessment and collection of outcomes {18a}

All investigators and coordinators will receive specialized training for data collection. Baseline assessments will be conducted before randomization. Any AE during neoadjuvant therapy will be assessed and managed by investigators and recorded timely. Tumor response after neoadjuvant therapy will be performed via enhanced CT using the response evaluation criteria in solid tumors, version 1.1 (RECIST 1.1), and the modified response evaluation criteria in solid tumors (mRECIST) in 2 weeks after neoadjuvant therapy. Perioperative data, including intraoperative information and postoperative complications which will be graded by Clavein-Dindo criteria, will be recorded before discharge.

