## Discussion

Therapy for HCC remains a formidable challenge, particularly in cases involving extremely large tumors, multiple primary tumors, or major vascular invasion—referred to as high-burden tumors [23–25]. Our study focuses on patients with a single huge HCC, which is recognized as an independent risk factor contributing to an increased risk of initial extra-hepatic recurrence [9, 23]. There has been an ongoing debate regarding the clinical staging and treatment strategy for large HCC [26–28]. According to the National Comprehensive Cancer Network (NCCN) Guidelines, liver resection is the preferred treatment for patients with any size of resectable solitary tumor, provided there is adequate liver function and liver remnant without major vascular invasion. The China Liver Cancer (CNLC) staging criteria classify a single large HCC as stage Ib (early stage), and liver resection is also the preferred treatment [29]. In contrast, the BCLC staging system suggests that single large HCCs often present with tumor-related symptoms, and HCC with symptoms should be staged as advanced disease [4]. Guidelines from BCLC recommend systemic therapy rather than liver resection for such cases. In line with the views of many scholars, we also believe that large tumors should not be considered a contraindication for surgical removal, particularly when patients have undergone effective and safe neoadjuvant treatment [25, 30, 31]. This not only increases the rate of surgical resection but also reduces the likelihood of postoperative recurrence, allowing patients to derive survival benefits from tumor resection.

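### Non-fatal surgical complications belong to no named outcome and are observed for unequal lengths of time in the two arms

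*Protocol article*

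**What the plan says.** Objectives {7} includes the aim to "explore the safety of neoadjuvant therapy regimen of TACE, camrelizumab, and apatinib". Outcomes {12} then sets the safety measure: "Safety outcomes encompass adverse events (AEs), defined as the occurrence of ≥ 3 grade hematological or non-hematological toxicities". The bracket that follows is open-ended: "including but not limited to liver dysfunction, hematological abnormalities, hypertension, diarrhea, proteinuria, hand-foot syndrome, etc". The other outcomes named there are recurrence-free survival (RFS), overall survival (OS) and pathological remission.

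Surgical complications appear elsewhere. Plans for assessment and collection of outcomes {18a} states that "postoperative complications which will be graded by Clavein-Dindo criteria, will be recorded before discharge". The same section places adverse-event assessment in the period of neoadjuvant therapy. The adverse-event row of Table 1 is marked at Weeks 1, 3, 5, 7 and 9 and at no later visit.

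Timing of surgery comes from Intervention description {11a}. Controls are operated on within a week of randomization. In the neoadjuvant arm camrelizumab stops at least 2 weeks, and apatinib at least 1 week, before the operation, and "Patients will receive surgery after neoadjuvant therapy if the disease is not assessed as progressive disease".

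**The concern.** Both arms are meant to have a major liver resection, in one of them after embolization and two drugs. Whether that pre-treatment makes the operation more hazardous is a central part of any safety comparison. The plan grades the relevant events but gives them no place among its named outcomes, and it stops recording them at a moment that is itself decided during care.

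A discharge cut-off makes the time at risk equal to the length of stay. If stays differ between arms or among the seven hospitals, recorded complication rates can differ when true rates do not, or agree when true rates differ. The trial is open-label, so those who decide on discharge know the arm. The adverse-event schedule could have served as a second source, but it covers the post-operative weeks of one arm and hardly any of the other.

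**Working it through.** No stated figure in the plan bears on this point, so the check is a timeline followed by two illustrations.

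**Timeline.** Inputs are Table 1 and Intervention description {11a}. I take Week k to start on day 7(k − 1) + 1, so Week 7 is day 43 and Week 9 is day 57, each with the stated window of ±3 days. I take a month as 30 days. Table 1 has a single adverse-event row, which I read as applying to both arms.

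1. Controls: surgery on days 1 to 7, last adverse-event visit at day 57. Scheduled post-operative cover is 57 − 7 = 50 to 57 − 1 = 56 days, or about 8 weeks at most.
2. Neoadjuvant arm: last camrelizumab at day 43, plus at least 14 days, gives surgery at day 57 or later. Scheduled post-operative cover is 57 − 57 = 0 days. With the windows at their most generous (dose at day 40, surgery at day 54, visit at day 60) it is 6 days.
3. If the two months of apatinib run in full from day 1, they end near day 61. Adding 7 days puts surgery at about day 68, after the last adverse-event visit.

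If the adverse-event row is meant for the neoadjuvant arm only, then neither arm has meaningful post-operative adverse-event visits, and the discharge-limited record is the only scheduled source.

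**Effect of a discharge cut-off.** Recorded rate = true rate × (1 − share of events after discharge). All inputs here are assumed. With a true rate of 20% in both arms:

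- 10% of events after discharge: 20% × 0.90 = 18%.
- 30% of events after discharge: 20% × 0.70 = 14%.

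The spurious difference is the true rate times the difference in shares. At a true rate of 20%, differences in shares of 0, 10, 20 and 30 points give 0, 2, 4 and 6 points. With 30 operated per arm, 18% versus 14% is 5.4 versus 4.2 patients, so about one patient.

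**Denominator.** Only operated patients can have a surgical complication, and in the neoadjuvant arm progression removes surgery by rule. The only resection proportion in the article is 94.4% (Background and rationale {6a}), from BCLC B/C patients given camrelizumab plus apatinib without TACE. Carried over purely as an illustration, 30 × 0.056 = 1.7 patients would not be resected. If 94.4% is 17/18 (assumed), the exact 95% interval is 72.7% to 99.9%, or 0 to about 8 of 30.

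**Which windows fit the existing visits.** Month 3 is about days 83 to 97 and Month 6 about days 173 to 187.

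- 30 days: controls close by day 7 + 30 = 37, before Month 3. The neoadjuvant arm, operated on at days 57 to 68, closes at days 87 to 98. Month 3 can come too early for them, but Month 6 does not.
- 90 days: controls close at days 91 to 97, while Month 3 may fall from day 83, so that visit often precedes the end of the window. Month 6 follows it in both arms (57 + 90 = 147 and 68 + 90 = 158, both before day 173).

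**The case against.** A reader might infer that the plan counts only drug-type toxicity, so that surgical harm cannot tell against the regimen at all. The document does not support that. The toxicity list is open-ended and names liver dysfunction, and Adverse event reporting and harms {22} puts any adverse event on the case report form. RFS is "defined as the time period from randomization to the first documented HCC recurrence or death from any cause", OS also counts every death from randomization, and efficacy is analysed by intention to treat. Operative deaths therefore count. What remains is non-fatal surgical morbidity.

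A second objection is that this is a condensed article. "The key secondary endpoints include pathological remission degree and OS" does not claim to be a complete list, and the full protocol is not shown. This has force against demanding a separate resection-rate endpoint: response is assessed before surgery, and CONSORT flow reporting would largely show who was not operated on. It does not reach the discharge cut-off, which is a rule the article states, or the end of the adverse-event row, which Table 1 fixes.

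A third tempting reading is that the Discussion contradicts the design by saying "This not only increases the rate of surgical resection but also reduces the likelihood of postoperative recurrence", although everyone enrolled is already resectable. In context the sentence belongs to a general argument that size alone should not rule out surgery. It is not a hypothesis of this trial and needs no correction on this account.

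Finally, Procedure for unblinding {17b} separates those who enrol and treat from those who collect data and assess outcomes. That helps the grading of complications. It does not make the discharge date, and so the window, independent of the arm.

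**Conclusion.** The point holds in a limited form. Non-fatal surgical complications belong to no named outcome. They are recorded over a window that varies with length of stay, and the scheduled adverse-event visits cover about 8 weeks after surgery in controls against roughly 0 to 6 days in the neoadjuvant arm. Surgical harm is therefore observed unequally between arms. The timeline rests on the visit schedule as printed and on the adverse-event row applying to both arms.

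The size of any bias cannot be derived from the documents. The 18% versus 14% example shows a mechanism on assumed inputs, and the count of 1.7 patients comes from a different population without TACE. Neither is an estimate for this trial. With at most 30 operated per arm the comparison will be descriptive in any case. That is a reason to make the windows equal, because a shift of one or two patients is visible at this size. The efficacy analysis is not affected.

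**What to change.** In Plans for assessment and collection of outcomes {18a}, replace the discharge cut-off with one fixed period counted from the date of resection, identical in both arms, that closes before a scheduled visit. Two versions work with the present schedule:

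- 30 days, captured at Month 3 for controls and by Month 6 for the neoadjuvant arm.
- 90 days, confirmed for every patient at the first scheduled visit after post-operative day 90. For controls this will often be Month 6, because Month 3 can fall before the period ends.

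In Outcomes {12}, name major Clavien-Dindo complications and death within that period as a safety outcome reported by arm. Show beside it the number of randomized patients in each arm who were not resected, with reasons, because complications can arise only in those operated on.

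The cost is a few more questions at visits already planned and one or two tables, with no extra patients or procedures. The safety figure may look less favourable, and events reported back at a later visit rely partly on recall and outside records, equally so in both arms only if the same questions are asked.
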